### Measures

Testing the primary hypotheses will require the measurement of several outcomes, namely patient engagement and perceived quality of medical care as well as self-efficacy and workload of staff. All questionnaires will be administered in Slovene. For questionnaires that have not yet been translated to this language and validated, we will use a standard procedure that involves translation and back-translation by qualified translators (32). Additionally, basic psychometric properties of the translated scales, such as internal reliability, will be tested prior to the main analyses.

Patient engagement will be measured with the Patient Health Engagement scale [PHE (33)], which consists of nine ordinal items. In the proposed study, we will convert the response format into a 5-point agreement scale ranging from “*completely disagree*” to “*completely agree*.” An example item is: “*Despite my illness, I know how to manage my life*.” The scale generally exhibits high correlations with concurrent measures, such as the Patient Activation Measure (34), and demonstrates solid reliability [test-retest and internal reliability (33)].

To measure the perceived quality of medical care, we will use the Perceived Quality of Medical Care scale [PQMC (35)]. The scale consists of six items (e.g., “*Medical care I have received was unsatisfactory/satisfactory*”), answered using a 7-point semantic differential scale. The scale is unidimensional and has previously exhibited excellent internal reliability [Cronbach α = 0.94 (36)].

The New General Self-Efficacy Scale [NGSE (37)] will be used to measure the extent to which employees believe they can achieve their goals. The NGSE is composed of eight items (e.g., “*I will be able to achieve most of the goals that I set for myself*”), which are answered on a 5-point agreement scale from “*strongly disagree*” to “*strongly agree*.” The overall score is then calculated by taking the average of all items. The scale is widely used in articles studying the adult population and generally exhibits high validity and reliability [Cronbach α = 0.86 (37)].

Lastly, employees’ workload will be measured with the Nasa Task Load Index [NASA TLX (38)], a very brief and widely used scale that assesses the perceived workload. The scale consists of six items (e.g., “*Temporal demand*”), answered on a 7-point scale ranging from “*very low*” to “*very high*.” The first three items will be slightly adapted to reflect the work in general instead of any one particular task. While each item alone provides useful and relevant information about different aspects of subjects’ experiences, the items can be combined into an overall score (39). Previous studies support the notion that the NASA TLX is a reliable and valid instrument also in the healthcare context [coefficient α = 0.72 (40)].

Answering the secondary objectives will require the assessment of additional outcomes, in particular, the percentage of non-urgent communication taken up by the social robot, time saved by human-robot interaction, and extra time of interaction provided to patients. Patients’ user experience and their ratings of each of the two types of nursing education (human/AI) and physiotherapy (human/AI) will also be assessed.

Most of these outcomes will not be measured with self-report questionnaires. During iterations with a socially assistive robot, the patients will be able to call for additional assistance and choose between human or AI assistance (by using one of two call devices). The number of calls will be recorded automatically, enabling us to calculate the ratio during analyses. Similarly, the number of actual interactions and the time spent for each encounter (with a human or AI) will also be recorded. Patients’ ratings of nursing education and physiotherapy delivered by a human/robot will be measured with a handful of self-construed items. It is worth noting here that both patients and staff will also be asked to fill out basic demographic questions.

Furthermore, patients will also fill out the User Experience Questionnaire [UEQ (30)]—the most widely adopted measure of user experience, which is already available in Slovene (41). It contains 26 items (e.g., “*unlikable/pleasing*”), which can form different subscores (i.e., perspicuity, efficiency, dependability, stimulation, and novelty) and the overall impression of the product. The subscales as well as the overall scale exhibit satisfactory internal consistency (for the overall score: coefficient α = 0.89).

### Data analysis

#### Preliminary analyses

We will use the IBM SPSS Statistics 28 program for statistical analysis. In the first step, we will clean the dataset and exclude all participants with more than 20% of missing values within any questionnaire. The remaining missing data will be analyzed to determine whether they are missing completely at random and, in case this is confirmed, replaced using the expectation-maximization algorithm. We will also perform basic psychometric analyses of the questionnaires, namely the analysis of reliability as internal consistency (coefficient α), and calculate the factor scores in accordance with the scoring instructions.

In the next step, we will perform basic descriptive analyses (means and standard deviations) and check the assumptions of the chosen statistical tests (such as the normality of the distribution assumption). This step will be followed by correlational analyses (to establish relationships between different variables) and inferential tests, whereby results with a *p*-value below 0.05 will be considered statistically significant.

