### Study design

The proposed study employs a between-within interaction design with multiple iterations. Patients and employees participating in the study will be recruited in a University Clinical Centre Maribor, Slovenia. The study will be carried out in 1-week intervals, followed by a 1-week washout period between each iteration. Overall, the study will be conducted over 2 years or less if the desired sample size is reached sooner.

Patients admitted to vascular and thoracic surgery wards for an elective (non-emergency) procedure will be screened for eligibility regarding the inclusion and exclusion criteria. Eligible participants will then be informed about the study characteristics and asked to fill out an informed consent form. Those who will consent to participate in the study will participate for 3–5 days. Depending on the week (see Figure 1), participants will be allocated to the standard care group (i.e., a control group that will not interact with a socially assistive robot) or standard care group with additional robot interactions. Participants from both groups will first be informed about the study and fill out the baseline questionnaires (demographic data, engagement, and perceived quality of care). Similarly, participants from both groups will be subjected to standard nursing education and general/respiratory physiotherapy delivered by nursing and physiotherapy staff. However, the patients allocated to the standard care group with additional robot interactions will additionally be subjected to nursing education and general/respiratory physiotherapy delivered by a socially assistive robot. Moreover, they will be able to call the robot for additional assistance (not related to nursing education and physiotherapy) during the whole study period. At the end of their participation, patients from both groups will be asked to fill out the questionnaires (engagement, perceived quality of care) for the second time. Patients from both groups will also be asked to rate the education and physiotherapy they received during the study period. Moreover, patients that will interact with a socially assistive robot, will also fill out the User Experience Questionnaire (30) at the end their participation.

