#### Analyses of patient-related outcomes

The patient-related outcomes, specifically patient engagement (H1, H3) and perceived quality of care (H2, H4), will primarily be analyzed with two separate mixed-design (split-plot) analyses of variance (ANOVA), with group as the between-subjects factor (2 groups: standard care, standard care with robot interactions) and time as the within-subjects factor (2 levels: T1 and T2; see Figure 1). Significant results will be followed up with *post hoc* tests using the correction to adjust for multiple testing. All results will be accompanied by effect sizes.

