#### Other analyses

The additional research questions will be answered descriptively (RQ1-RQ3, RQ5) or using the Pearson correlation coefficient (RQ4).

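### As written, the 20% missing-data rule could remove robot-arm patients from H1–H4 because of blanks on a questionnaire that control patients never receive

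*Protocol article*

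**What the plan says.** The rule is in the protocol article under Data analysis, Preliminary analyses. It opens with "In the first step, we will clean the dataset", and in that same step the team will "exclude all participants with more than 20% of missing values within any questionnaire". Descriptive statistics, assumption checks and inferential tests follow. Gaps that survive the rule are tested for being missing completely at random and, "in case this is confirmed, replaced using the expectation-maximization algorithm".

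Study design says who completes what. At the end of participation, "patients from both groups will be asked to fill out the questionnaires (engagement, perceived quality of care) for the second time". Both groups also rate the education and physiotherapy they received. In addition, "patients that will interact with a socially assistive robot, will also fill out the User Experience Questionnaire". Measures says of the UEQ: "It contains 26 items". It gives PHE nine items and PQMC six.

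H1–H4 concern engagement and perceived quality of care only. Under Analyses of patient-related outcomes these "will primarily be analyzed with two separate mixed-design (split-plot) analyses of variance (ANOVA"), with group and time as factors. User experience is RQ5, which Other analyses answers descriptively. The article nowhere exempts the UEQ from the 20% rule or confines its exclusions to RQ5.

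**The concern.** The unit removed is the participant, not the affected scale, and the trigger is not limited to the instrument under analysis. Read with the questionnaire schedule, this makes membership of the H1–H4 analysis set depend on arm. Robot patients face one further instrument, completed after allocation and about the intervention itself, on which too many blanks delete otherwise complete outcome data.

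Allocation is already by calendar week rather than by randomisation, so the groups' comparability is not protected by design, and an avoidable second source of selection is unwelcome. H1 and H2 (change within the robot arm) would be affected through who remains in that arm. H3 and H4 (difference in change between arms) would be affected because the other arm has no matching exclusion.

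The same wording also links the two outcomes in both arms: too many blanks on one of PHE and PQMC discard complete data on the other.

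**Working it through.** **1. Number of blanks that triggers exclusion** (item counts from Measures; smallest whole number above 20%)

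| Scale | Items | 20% of items | Blanks that exclude | Share | Who receives it |
|---|---|---|---|---|---|
| PHE | 9 | 1.8 | 2 | 22% | both arms, twice |
| PQMC | 6 | 1.2 | 2 | 33% | both arms, twice |
| UEQ | 26 | 5.2 | 6 | 23% | robot arm, once |

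Five UEQ blanks (5/26 = 19%) exclude nobody. Leaving demographic and rating items aside, a control patient answers 2 × (9 + 6) = 30 items and a robot patient 30 + 26 = 56. The extra 26 do not enter H1–H4.

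**2. The plan's own sample size**

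Inputs from Participants and recruitment: f = 0.15, α = 0.05, power 0.80, 2 groups, 2 measurements, about 90 patients. Assumed, because not stated: pre-post correlation ρ = 0.5 and 45 patients per arm.

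For the within-between interaction, λ = f² × N × m / (1 − ρ) = 0.0225 × 90 × 2 / 0.5 = 8.1, with 1 and 88 degrees of freedom. Power is 0.804 (0.795 at N = 88), so 90 is reproduced. At other correlations the required N would differ: 126 at 0.3, 72 at 0.6.

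The same test is a two-sample t-test on change scores, where λ = d² × N / 4. Setting 0.09N = d²N/4 gives d = 0.60 SD of change. That figure therefore depends on ρ = 0.5.

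**3. Power after one-sided exclusion**

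The noncentrality is 0.60 × √(n₁n₂/(n₁ + n₂)), with the true difference held at 0.60. The exclusion rates are assumptions.

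| Robot patients excluded for UEQ blanks | Control / robot | Noncentrality | Power |
|---|---|---|---|
| none | 45 / 45 | 2.85 | 0.804 |
| 5% | 45 / 43 | 2.81 | 0.794 |
| 10% | 45 / 40 | 2.76 | 0.779 |
| 20% | 45 / 36 | 2.68 | 0.755 |

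**4. Bias**

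Let a fraction q of the robot arm be excluded, with mean change lower than the rest by δ. The whole-arm mean is the retained mean minus qδ, so exclusion raises the arm's mean, and the group difference, by qδ.

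- Low end: 0.05 × 0.5 = 0.025 SD, which is 0.025/0.60 = 4% of the planned effect.
- High end: 0.20 × 1.0 = 0.20 SD, which is 0.20/0.60 = 33%.
- δ = 0: no bias. δ negative: the robot arm is made to look worse.

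**5. A second model for the same quantity**

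Suppose a latent tendency to complete the UEQ correlates r with change, and the lowest fraction q is excluded. The shift is r × φ(z_q)/(1 − q).

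- r = 0.3, q = 10%: 0.3 × 0.1755/0.9 = 0.058 SD.
- r = 0.5, q = 20%: 0.5 × 0.280/0.8 = 0.175 SD.

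With no true effect, and treating the SD as unchanged by the exclusion, the two-sided type I error in these two cases is about 0.06 and 0.12 instead of 0.05. Both r and q are assumptions.

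**The case against.** The strongest reply is that this is one condensed sentence in a journal article, that it does not name the UEQ, and that the authors may have meant exclusion analysis by analysis. That is possible, and it is why the point says could rather than will. But the article fixes the rule affirmatively, with the participant as the unit and any questionnaire as the trigger. An analyst who followed the text would make the asymmetric exclusion, so this is not detail merely left to a fuller document.

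Several stronger readings are tempting and are not supported:

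- **That the robot arm will be selectively improved.** Nothing in the article gives a UEQ non-completion rate or ties blanks to dislike of the robot. Fatigue or discharge timing could equally explain them. The 0.20 SD figure needs both assumed extremes at once.
- **That any incomplete UEQ removes a patient.** It takes 6 or more blanks.
- **That staff who miss a later wave drop out of the T1/T2 test.** The rule speaks of missing values within a questionnaire. That wording fits item gaps at least as well as an unreturned form.
- **That the expectation-maximization step is a comparable defect.** Two blanks already exclude on PHE, PQMC and both staff scales (2/8 for self-efficacy, 2/6 for workload). At most one item per primary scale per administration is left to fill, so any understatement of standard errors should be minor. What happens if missingness is found not to be completely at random is detail an article commonly leaves to the full plan.
- **That the mixed ANOVA must be replaced.** Confining the rule to the scale under analysis cures the asymmetry without changing the model.

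The power loss is also small, as the objection would say. What stands is the arm-dependent exclusion itself.

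**Conclusion.** The concern holds as a defect in the wording of the rule. Taken as written, it allows post-allocation exclusion from H1–H4 on the strength of an instrument that only one arm receives and that those hypotheses do not use. It also lets gaps in one primary outcome delete complete data on the other. This follows from the text alone and needs no assumption.

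The size does need assumptions. With 5–20% of robot patients excluded and their change 0.5–1.0 SD below the rest, the group difference is inflated by about 0.03–0.20 SD, or 4–33% of a planned 0.60 SD. Power falls from 80% to 79–76%. The 0.60 SD and the power figures rest on a pre-post correlation of 0.5 and equal arms, neither of which is stated. Selection is the larger concern and power the smaller. Whether there is any bias, and in which direction, cannot be settled from the documents.

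**What to change.** Reword the rule under Preliminary analyses so that:

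1. the 20% threshold is applied separately for each hypothesis, to the scale and the time points that the hypothesis uses;
2. missing UEQ items, or missing ratings of education and physiotherapy, never remove a patient from H1–H4;
3. exclusions are reported by arm, with the scale that caused them.

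UEQ gaps then cost H1–H4 nothing: the example stays at 45/45 with power 0.804. The planned ANOVA and sample size are unchanged and no new data are needed. The cost is a few lines of text, and analysis sets that may differ slightly in size between engagement, quality of care and user experience.

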#### Analyses of employee-related outcomes

The employee-related outcomes, namely self-efficacy (H5) and workload (H6), will be analyzed with two separate Paired-samples *t*-tests, with time as the within-subjects factor (2 levels: T1, T2; see Figure 2). All results will be accompanied by effect sizes.

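### Imputation depends on confirming that data are missing completely at random, no method is named otherwise, and the 20% rule removes whole participants under any mechanism

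*Protocol article*

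**What the plan says.** The protocol article, under Data analysis, Preliminary analyses, sets two steps in order.

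1. The team will "exclude all participants with more than 20% of missing values within any questionnaire". This comes before any check of the missingness mechanism and does not depend on one.
2. The second step covers only what the first leaves over. The purpose given for examining those values is to "determine whether they are missing completely at random and, in case this is confirmed, replaced using the expectation-maximization algorithm". Nothing is said about what happens if MCAR is not confirmed.

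The patient outcomes (H1 to H4) then go into "two separate mixed-design (split-plot) analyses of variance (ANOVA"), with two groups and two time points. The staff outcomes (H5, H6) go into "two separate Paired-samples *t*-tests". On software the plan says: "We will use the IBM SPSS Statistics 28 program for statistical analysis".

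**The concern.** The condition on imputation is badly chosen for three reasons.

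- **It cannot be met.** A test of MCAR can reject it. A non-significant result does not establish it.
- **It is tied to the wrong assumption.** EM is valid under MAR, where missingness may depend on observed data such as group, T1 score or the other items. Under MCAR the complete cases are already a random subset, so imputation gains precision but removes no bias.
- **The other branch is empty.** Split-plot ANOVA and paired t-tests need a score at both occasions. With no method named, they would by default use complete scores only, which is open to bias if missingness depends on observed data.

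The first step raises a separate problem. A patient who completes T1 but returns no T2 questionnaire has 100% missing there and is excluded, along with the T1 data. The rule also covers any questionnaire, and only robot-arm patients fill out the User Experience Questionnaire (UEQ). Read literally, a robot-arm patient can be lost from H3 and H4 for blanks in the UEQ, while no control patient can be lost that way.

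**Working it through.** **1. The plan's own figure.** Participants and recruitment gives f = 0.15, alpha 0.05, power 0.80 and about 90 patients. For the within-between interaction, lambda = N × m × f² / (1 − rho), with m = 2 and 1 and N − 2 degrees of freedom. The T1–T2 correlation rho is not stated. With rho = 0.5 (assumed), lambda = 90 × 2 × 0.0225 / 0.5 = 8.1 and power is 0.804, so 90 is reproduced. In a 2 × 2 design f = 0.15 means interaction cell effects of ±0.15 SD, hence a difference in change of 4 × 0.15 = 0.6 SD. At rho = 0.5 the SD of change is 1, and the standard error with 45 per arm is √(2/45) = 0.21 SD.

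**2. What the MCAR condition can reach.** Item counts are from Measures: for the engagement scale (PHE), "which consists of nine ordinal items"; for perceived quality of care (PQMC), "The scale consists of six items (e.g., “*Medical care I have received was unsatisfactory/satisfactory"; eight for self-efficacy (NGSE), six for workload (NASA TLX) and 26 for the UEQ.

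| Scale | Items | Most blanks kept | First count excluded |
|---|---|---|---|
| PHE | 9 | 1 (11.1%) | 2 (22.2%) |
| PQMC | 6 | 1 (16.7%) | 2 (33.3%) |
| NGSE | 8 | 1 (12.5%) | 2 (25.0%) |
| NASA TLX | 6 | 1 (16.7%) | 2 (33.3%) |
| UEQ (robot arm only) | 26 | 5 (19.2%) | 6 (23.1%) |

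For the four primary scales the condition concerns one blank item per occasion. Six blank UEQ items would exclude a robot-arm patient.

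**3. How many patients that could be.** The article gives no missing-data rate. Assume 2% of items are blank, independently, over two occasions.

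- PHE: at least one blank, 1 − 0.98^18 = 30.5%. The 20% rule keeps 97.4% and 69.5% are complete, so 97.4 − 69.5 = 27.9% have a blank and are kept.
- PQMC: 1 − 0.98^12 = 21.5%; kept with a blank, 98.9 − 78.5 = 20.4%.

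If only complete cases were analysed, 90 would fall to about 63 for PHE (power 0.65) and 71 for PQMC (power 0.70). At 0.5% blank the numbers are 82 and 85 (power 0.77 and 0.78); at 3% they are 52 and 62 (power 0.56 and 0.64). Blanks of this kind are MCAR, so the plan would normally impute them. The figures show how many patients hang on the condition, not a loss the plan predicts.

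**4. Bias in the unaddressed branch.** A deliberately strong MAR scenario was simulated (400 runs, N = 90, no true interaction). One T2 item was blank for about 33% of the robot arm and 5% of controls, depending on the other T2 items. Dropping the incomplete cases gave a false difference in change of 0.21 (SD of change 1.09, so about 0.2 SD) and 13% rejections at the 5% level. EM gave 0.00 and 5%.

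**5. Bias from losing patients without T2.** Assume no true effect and, in the robot arm only, P(T2 missing) = expit(−1.6 − T1), with T1 standard normal. Then 20.7% lack T2 and the completers' mean T1 is 0.179 SD. The expected change given T1 is −(1 − rho) × T1, so the bias in the difference in change is −(1 − rho) × 0.179:

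- rho = 0.5: −0.089 SD, or 0.089 / 0.6 = 15% of the planned difference;
- rho = 0.7: −0.054 SD, or 0.054 / 0.6 = 9%.

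The sign reverses if patients with high T1 leave. These patients go at step one, so deleting the MCAR condition alone would not change this figure.

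**The case against.** A reader might infer that the plan drops incomplete cases whenever MCAR is not confirmed, and so uses deletion exactly when deletion is invalid. The article does not say this. The branch is unwritten, and scoring from available items would also fit the text, since NGSE is described as an item average. Failing an MCAR test also does not make every complete-case analysis biased, and the one deletion rule that is written applies under MCAR too. That reading is therefore not supported.

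A reader might also attach the dropout bias in step 5 to the MCAR condition. It belongs to the 20% exclusion and to complete-case analysis.

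It is fair to add that the effect is modest. Patients are followed for only 3–5 days, no dropout rate is given, and 0.05 to 0.09 SD is under half of the 0.21 SD standard error. A full analysis plan might also fill the empty branch.

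What remains does not depend on that plan. The MCAR condition and the person-level exclusion are both fixed in the article's text, and both are poor choices as written.

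**Conclusion.** The point holds in a limited form. Making EM conditional on confirmed MCAR is a mistaken rule: the condition cannot be established, EM does not need it, and no method is named for the case where one is most needed. Its reach is small, at most one blank item per primary scale per occasion. The person-level 20% exclusion is likely the larger source of selection, because it removes every patient without T2 under any mechanism and, read literally, can act on one arm alone through the UEQ.

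The plausible bias from that exclusion is about 0.05 to 0.09 SD against a planned 0.6 SD. This rests on an assumed 20.7% loss in one arm, dependence on T1 with a logit slope of −1 per SD, and rho of 0.5 to 0.7. The change is worth making, but the flaw would not by itself overturn the trial's conclusions at that size.

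**What to change.** 1. Delete the MCAR condition. Treat item blanks within the 20% tolerance by one rule in all cases: EM or another MAR-based imputation within the scale, using group and the other time point.
2. Apply the 20% rule per questionnaire and occasion. Above it, set that score to missing and keep the participant. UEQ blanks then affect only UEQ results. Without this change, patients lacking T2 never reach the model in item 3.
3. Test H3 and H4 with a likelihood-based mixed model (SPSS MIXED; group, time, group × time; unstructured covariance), so that patients with T1 only contribute under MAR. Report the complete-case ANOVA as a sensitivity analysis.

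The cost is analysis wording only. The software is already named, no new data are needed, and with complete data the interaction test is unchanged.
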